## Abstract

**Background:**

Tobacco use is the most preventable cause of morbidity and mortality in Australia. Comprehensive tobacco control has reduced smoking rates in Australia from approximately 34 per cent in 1980 to 15 per cent in 2010. However, 46 per cent of Aboriginal and Torres Strait Islander people (Indigenous Australians) smoke on a daily basis, more than double the rate of non-Indigenous Australians. The evidence of effective tobacco control strategies for Indigenous Australians is relatively scarce. The aim of this study is to (i) explore the influences of smoking in Indigenous Australian people and to (ii) help inform and evaluate a multi-component tobacco control strategy. The study aims to answer the following questions: - do individuals' social networks influence smoking behaviours; - is there an association between various social and cultural factors and being a smoker or non-smoker; and - does a multi-component tobacco control program impact positively on tobacco behaviours, attitudes and beliefs in Indigenous Australians.

**Methods and design:**

Our prospective study will use a mixed-method approach (qualitative and quantitative), including a pre- and post-test evaluation of a tobacco control initiative. The study will explore the social and cultural context underlying Indigenous Australian tobacco use and associated factors which influence smoking behaviour. Primary data will be collected via a panel survey, interviews and focus groups. Secondary data will include de-identified PBS items related to smoking and also data collected from the Quitlines call service. Network analysis will be used to assess whether social networks influence smoking behaviours. For the survey, baseline differences will be tested using chi^2^ statistics for the categorical and dichotomous variables and t-tests for the continuous variables, where appropriate. Grounded theory will be used to analyse the interviews and focus groups. Local Aboriginal community controlled organisations will partner in the study.

**Discussion:**

Our study will explore the key factors, including the influence of social networks, that impact on tobacco use and the extent to which smoking behaviours transcend networks within the Indigenous Australian community in the ACT. This will add to the evidence-base, identifying influential factors to tobacco use and the effectiveness and influence of a multi-component tobacco control strategy.

## Background

Tobacco use is the most preventable cause of morbidity and mortality within Australia [1]. While Australia is a world leader in comprehensive tobacco control, including the recent implementation of the world’s first plain packaging policy through the Tobacco Plain Packaging Act 2011, there is room for improvement, especially in certain sub-populations [1,2]. Tobacco control policies in Australia have resulted in reducing the smoking rates from approximately 34 per cent in 1980 to 15 per cent in 2010 [1,2]. However, this is not the case for all population groups with 46 per cent of Indigenous Australians smoking on a daily basis, more than double the rate of non-Indigenous Australians [1]. Indigenous Australians have a notable history with tobacco [3,4]. For example, tobacco provided an incentive for labour with many Indigenous Australians continuing to receive rations of tobacco from employers up to the 1960s [4-6]. The high rates of smoking among Indigenous Australians [7-10], is the single most significant contributor to premature deaths (one in five) among Indigenous Australian people. Tobacco smoking also contributes significantly to shorter life expectancy when compared with non-Indigenous Australians [11].

It is well established that there are a number of cultural and socio-environmental factors that influence mainstream tobacco use [12-19]. Evidence has indicated that peer associations can impact on behaviours, including the initiation and cessation of smoking predominantly among young people, and in relation to substance use [20-22]. Smoking can be a mechanism to maintain and strengthen kinship bonds and social relationships and to enhance a sense of belonging and social cohesiveness [23-25]. Research has investigated socially, culturally and politically appropriate approaches to behaviour change in relation to tobacco use [26-31] with social networks theorised to have a significant influence in the behaviour change processes [32-36]. However, our understanding of attitudes, behaviours and the way in which social networks influence and operate in relation to smoking behaviours in Indigenous Australian communities is very limited. Our study aims to investigate various social and cultural factors and their influence on smoking behaviours, attitudes and beliefs. Measures of smoking behaviour include smoking status and levels of tobacco consumption, while indicators of attitudes and beliefs include:

•how often a respondent thinks about ‘enjoying smoking’;

•if respondents’ perceive cigarette brands to be more prestigious or more harmful than other cigarette brands; or

•the perceived level of importance of a number of statements, such as ‘smoking may interfere with my performance’, ‘smoking may make me vulnerable and put me at risk for harm’ or ‘my culture does not allow smoking’.

The study will use a number of underpinning theories, including the theory of triadic influence, social network analysis, diffusion of innovations theory and homophily in order to triangulate evidence and add validity to our interpretation of this complex issue [37,38]. This will assist to develop our ability to design and implement optimal, culturally appropriate and effective tobacco control targeting Indigenous Australians [39,40].

### Research questions

The research will investigate the impact of tobacco control programs and policies among the Indigenous Australian population in the ACT region and ask the following research questions:

•do individuals' social networks influence smoking behaviours?

•is there an association between various social and cultural factors and being a smoker or non-smoker?

•do tobacco control programs in the Australian Capital Territory (ACT) impact on tobacco behaviours, attitudes and beliefs in the Indigenous population?

### Underpinning theories

In recent times there has been a strong commitment to address the high rates of smoking in the Indigenous Australian population through the Close the Gap campaign, the National Tobacco Strategy 2012–2018, the National Partnership Agreement on Closing the Gap in Indigenous Health Outcomes and the National Healthcare Agreement [41-47]. The National Healthcare Agreement has set the target of closing the life expectancy gap for Indigenous Australians within a generation (2030) and to halve the 2009 Indigenous smoking rate by 2018 [42]. The ACT Government made a further commitment to reduce smoking rates among Indigenous Australians through the development of the ACT Aboriginal and Torres Strait Islander Tobacco Control Strategy 2010–2014 [41].

The Strategy recognises that while there is evidence regarding the prevalence of smoking in the Indigenous Australian community, reports on the effectiveness of tobacco control initiatives for Indigenous Australian people and communities are scant [48]. Much of the work to date in Indigenous Australian tobacco control draws two central tenets:

1. tobacco control is best delivered in the community setting; and

2. to be effective participation must be based in the social, work or family environment [41].

Evidence indicates that the social network structure can influence health behaviour and that normative and other peer influences transmitted through network ties can shape risk behaviours [13,49]. A better understanding of the relationship between Indigenous Australian social networks and smoking is required [13]. Our research will utilise four associated underpinning theories in a prospective study of smoking behaviours of Indigenous Australian people [37,38,50].

### The theory of triadic influence

The theory of triadic influence describes three streams of influence in relation to tobacco use:

1. cultural/environmental influences - community characteristics, media influences, legislation and policy;

2. social-situational or normative influences - including parent and peer influences and their attitudes, use of tobacco and characteristics of relationships; and

3. individual, person or biological influences - genetic, biological, personality variables, gender, ethnicity and age [51,52].

As illustrated in Figures 1 and 2, the theory outlines three variables across the three streams of influence; ultimate, proximal and distal. Proximal factors influence behaviours directly (e.g. smoking related attitudes and beliefs) in contrast to ultimate factors, which are beyond the control of individuals, indirectly placing them at risk of smoking behaviour (e.g. broader cultural, social and biological influences) [51,52]. Given this context and based on research in relation to smoking among young people in the USA [20,21], it is expected that similar attitudes and beliefs will be reflected in participants’ broader social networks. Furthermore, it is this evidence and context that leads us to social network analysis, diffusion of innovations theory and homophily as directly and indirectly relevant theories regarding smoking among Indigenous Australian communities.

**Figure 1 F1:**
[figure not shown]
**The theory of triadic influence.** Source: Modified from [35,51].

**Figure 2 F2:**
[figure not shown]
**The theory of triadic influence.** Source: Modified from [35,51].

### Social network analysis

A network is a structure made up of nodes (individuals, organisations, etc) that are connected together by ties (relations such as friendship, kinship, exchanges, activities, etc) [53-55]. Social network analysis provides a way of characterising and investigating such structures, including through network visualisation (using graphic display as illustrated in Figure 2), structural analysis and statistical analysis [55-58]. If participants' networks influence smoking behaviours, it would be expected that participant’s networks would share similar smoking behaviours. Thus, we would compare the observed network to a simulated network with the same network characteristics, including the same overall rate of smoking prevalence, but with the incidence of smoking randomly distributed across the network [59]. If clustering is occurring among smokers or non-smokers, then the probability that a participant who smokes has a network contact who is also a smoker should be higher in the observed network than in the simulated network [21,60]. Perceived proportion of peers who smoke will be measured by analysing the respondents’ perceptions of how many of their peers smoke (about what proportion (%) of your friends and acquaintances use tobacco?) and respondents’ perceptions of how many of their five closest friends and family are regular smokers (thinking about your five closest friends and family, how many of these five are regular smokers?).

Wellman [61] outlined that individuals’ behaviour is best predicted by examining their social network and ecological characteristics in which they are entrenched; not intrinsic factors such as attitudes, drivers or demographic characteristics. Furthermore, nothing can be accurately understood in isolation or without context [61]. Therefore, these structures―social networks of interconnected individuals―and characteristics can be useful to develop, tailor and implement health promotion and public health programs, including tobacco control [62]. Within the Indigenous Australian context, tobacco was seen as a prestigious substance and has been a highly valued commodity [3,7,63]. Smoking has been a central mechanism for relationships, assisting to maintain and reinforce kinship bonds and social relationships and also used as a practical currency and an incentive prior to Indigenous Australian peoples full engagement with the cash economy in the late 1960s [4-6]. As a result, the primary data collection in this study is expected to reflect the importance of social and cultural norms regarding smoking and the influence of social networks. It is anticipated that similar behaviours and beliefs about smoking will resonate among participant networks [23-25].

### Diffusion of innovations theory

The diffusion of innovations theory is the most prominent behavioural application of network analysis and has been widely used in public health; explaining the steps, processes and how new ideas and practices spread within and between communities [64]. Given the context that has influenced the high rate of smoking among the Indigenous Australian community and the evidence regarding the social role of tobacco [3,4,7,63], it is logical that the diffusion of innovations theory will provide the theoretical foundations to investigate how social networks can affect behaviour and behaviour change around smoking [64]. Diffusion of behaviours and effective programs are a significant challenge for public health, health promotion and subsequently, tobacco use [65,66]. Ryan and Gross [67] identified significant influence on social contacts, interactions and interpersonal communication on the adoption of new behaviours. New behaviours and practices may originate in a community and can be disseminated and diffused through the community where they originated and beyond through numerous communication channels, such as mass media, social media, interpersonal channels and electronic communication [58,68,69]. As a result, it is evident that factors influencing diffusion are not static factors of behaviour change. Influential factors are generally dynamic interactions that occur between a number of factors, individuals and the environment [64]. If effective public health programs, products and practices are not effectively disseminated and diffused, they will not achieve optimal impact to improve public health [64].

### Homophily

Individuals' social networks can be homogeneous with regard to socio-demographic characteristics, intrapersonal factors or behaviours, such as smoking; “similarity induces homophily” [70]. Homophily is the principle that interaction between similar individuals or organisations occurs more frequently than among dissimilar individuals or organisations [70]. This is related to the process of peer socialisation, whereby people take on the values and behaviours of the ‘group’ in order to be accepted [71]. In the context of the social norms around tobacco among Indigenous Australian people and the high rate of smoking, homophily is a sound underpinning for this research. McPherson and colleagues [70] indicated that behavioural, cultural, genetic or other information that flows through networks is more likely to be clustered. In alignment with the theory of triadic influence, this may be one factor for the inconsistent effect of tobacco control on smoking rates of different population groups [70].

### Synthesis: underpinning theories

Our research will use triangulation to enhance the validity and generalisability of the study by increasing the likelihood that the findings and interpretations will be credible and dependable [37,38,50,72]. Triangulation will strengthen the research and lead to a more comprehensive understanding of the complex issue of tobacco use, using multiple disciplinary and theoretical lenses to view and investigate the research findings and data sets [37,50,73].

Triangulation was originally used in the health and social sciences by psychologists Campbell and Fiske [74] using multiple tests to measure the same constructs to look for convergent validity. It has been used in a broad range of research related to health sciences and within the public health and health promotion sphere [75-80]. Our research will use these underpinning theories, data sources and analyses to enhance the validity of the study [37,38,50,72]. There is limited evidence regarding effective tobacco control for Indigenous Australian people and insufficient evidence in relation to network analysis in this area. It is this gap in knowledge that motivates the research questions. Therefore, this research will strengthen our understanding of the factors that influence smoking, including exploring cultural and social beliefs and attitudes.

## Methods/design

### Aim and objectives

The objectives of the research are to answer the following questions:

•do individuals' social networks influence smoking behaviours;

•is there an association between various social and cultural factors and being a smoker or non-smoker; and

•do the tobacco control programs under the Action Area 1 of the ACT Aboriginal and Torres Strait Islander Tobacco Control Strategy 2010–2014 (this includes smoking cessation groups, youth and community health promotion programs and education campaigns) impact on tobacco behaviours, attitudes and beliefs in the Indigenous Australian population.

We will undertake surveys, focus groups and interviews in two waves approximately 12 months apart; pre- and post-implementation of the multi-component tobacco control initiative. This will assist to identify commonalities and disparities, assessing the effectiveness of program and further exploring socio-environmental mechanisms that influence tobacco use, attitudes and behaviours [81,82]. Data will be collected via:

1. surveys;

2. interviews;

3. focus groups; and

4. use of existing de-identified health data, for example, the Talking About the Smokes survey data, data regarding relevant Pharmaceutical Benefit Scheme (PBS) item listings related to smoking (e.g. item codes for nicotine replacements) and Quitlines call data and volume.

### Data collection instruments: survey, interview guide and focus group guide

The data collection instruments were developed based on valid, reliable and tested surveys, including the:

•Australian Census;

•Fagerström Test for Nicotine Dependence;

•National Aboriginal and Torres Strait Islander Social Survey questionnaire;

•National Aboriginal and Torres Strait Islander Health Survey questionnaire; and

•National Drug Strategy Household Survey questionnaire [2,83-88].

The network analysis components are adapted from previous studies of social networks by Alexander et al. [89], De Lange et al. [90] and others [14,90-94]. Each instrument includes social network questions in relation to the characteristics of the participants’ friends, family and people that reside in their household. The data collected, including responses to the network questions, will provide invaluable insight into the centrality of participants, their relationships/networks and smoking behaviours and beliefs. Network analysis will also be supported through recruitment via convenience and snowball sampling.

#### The sample population

Participants will generally be Indigenous Australian people residing in the ACT region. The sample will include adults and children (12 years and above). Young people have been included to reflect the younger Indigenous Australian demographic profile and the early uptake of tobacco use in children [95,96].

#### The sampling frame

Our primary points of recruitment in the ACT include the ACT Indigenous Network, an Aboriginal Community Controlled Health Organisation, an Aboriginal Community Controlled Youth Centre, local community events, and a number of other Indigenous Australian organisations and their networks. These organisations will be used to help recruit participants via convenience and snowball sampling [37,97]. After potential participants receive the study information sheet and voluntarily make contact with the researcher to participate, the potential participants will be asked to provide informed consent prior to participating in the study.

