### The survey

The survey (paper and online versions) will collect quantitative data on individuals’ behaviours, attitudes and ecological characteristics, including social network data to explore the influence of family and peers. Therefore, while the participants are the source of all information, there are two different sampling units: the individual respondent; and the relationships/networks [98]. Objectives of the survey will include the domains; demographics; socio-economic status, and will explore:

•factors that influence smoking, including cultural and social beliefs and attitudes related to smoking, smoking cessation and non-smoking;

•attitudes, knowledge, beliefs and awareness in relation to smoking behaviours;

•nicotine dependence (Fagerström Test for Nicotine Dependence) [83,84];

•the impact of tobacco control programs and campaigns, including awareness and recognition;

•smoking, quitting and non-smoking behaviours; and

•family, friends and peers influence in relation to smoking behaviours.

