#### Analysis

Statistical and social network analysis will be used to characterise and describe the results, using multiple imputation of missing data prior to analysis [55,81]. In examining the association between various social factors, data will be aggregated and entered in SPSS, UCINET, NetDraw and Microsoft Excel for statistical and network analysis. In assessing if tobacco control programs have influenced behaviours, attitudes and beliefs in relation to smoking, analysis will incorporate common descriptive statistics and comparisons between the pre- and post-intervention groups. For example, comparisons between the pre and post-intervention groups will use X^2^ (categorical distributions) and T-tests (interval or ratio data). Bivariate associations between variables will be tested by X^2^ in analysing smoking type (daily smoker, occasional smoker, light smoker, social smoker, ex-smoker and non-smoker) by gender, age group, income group, education level, etc. Wilcoxon rank sum tests or Spearmans rank correlations will also be used depending on whether the variables are binary or ordinal. Multiple regression will be used to test whether individual variables are independently predictive of outcomes. Comparisons will be conducted across and between the sub-groups for both pre- and post-intervention [81,99]. Analysis will also include examining the data from the Fagerström Test for Nicotine Dependence questions in the survey for reductions in means scores, indicating reduced nicotine dependence. The higher the accumulated Fagerström score per participant, the more intense the participant’s physical dependence on nicotine [84]. Computations will be undertaken using SPSS and Microsoft Excel [83-85].

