Social network analysis will be used to assess if individuals' social networks influence smoking behaviours. Network analysis will include exploring smoking and non-smoking networks constructed from the survey data and complemented by the qualitative data collection. This will include network visualization, structural analysis and statistical analysis [55]. Several network level measures of structure will be assessed, including clustering, network size, number of ties and reciprocity [55,58]. To study the clustering of smoking behaviour, we will compare the observed network at each data collection point to a simulated network with the same network characteristics, including the same overall rate of smoking prevalence, but with the incidence of smoking randomly distributed across the network [59]. If clustering is occurring among smokers or non-smokers, the probability that a participant who smokes has contact with other smokers should be higher in the observed network than in the simulated network [21,60]. These network metrics will be used to provide a descriptive presentation of the network/s and any changes over time. The pre- and post-test survey will be analysed using Analysis of Variance (ANOVA) on the gain scores and Analysis of Covariance (ANCOVA).

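### Respondents recruited partly by snowball are tested as if independent, so p-values for socially patterned predictors of smoking will tend to be too small

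*Protocol article*

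**What the plan says.** **Recruitment.** The sampling frame section lists several community entry points and states: "These organisations will be used to help recruit participants via convenience and snowball sampling". The section on data collection instruments shows that the linkage is intended: "Network analysis will also be supported through recruitment via convenience and snowball sampling". The survey section recognises that "there are two different sampling units: the individual respondent; and the relationships/networks".

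**Expected similarity.** The social network analysis section says: "It is anticipated that similar behaviours and beliefs about smoking will resonate among participant networks". The homophily section adds that networks can be homogeneous in socio-demographic characteristics as well as in behaviours such as smoking.

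**Tests.** The survey's analysis section compares the pre and post groups by chi-square and t-tests. For associations it says "Bivariate associations between variables will be tested by X^2^ in analysing smoking type" by gender, age group, income group, education level and so on. It adds rank sum tests and rank correlations, and then: "Multiple regression will be used to test whether individual variables are independently predictive of outcomes". It ends with ANOVA on gain scores and ANCOVA. It names no cluster-robust variance, random effect or network-autocorrelation term.

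**Sample size.** A minimum of 102 is given for 90% power to detect a 10 per cent reduction from 36% smoking. No design effect is mentioned.

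**The concern.** The design and the study's own hypothesis both point to correlated responses among linked participants, whereas the named individual-level tests assume that there is no such correlation. If the answer to the first research question is that networks do shape smoking, the standard errors used for the second question (social and cultural factors and being a smoker) are not valid as planned.

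At stake is the error rate of those association tests. Income, education and age group are candidates to cluster along the same social ties as smoking. When predictor and outcome both cluster, an ordinary chi-square test or regression gives p-values that are too small, and chance associations are reported too often. The planned sample also carries less information than its head count for any estimate that clusters.

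**Working it through.** **The plan's own figure.** The sample size section gives 102, 90% power, 36% at baseline and a 10 per cent reduction. It does not state alpha, sidedness, whether the reduction is absolute or relative, or whether 102 is per wave or in total. I assume two-sided alpha of 0.05. For two independent groups, 36% against 26% needs 448 per wave, and 36% against 32.4% needs 3,647 per wave. With 102 per wave, power for 36% against 26% is 33.8%. A near match (101) comes only from a paired McNemar calculation in which nobody takes up smoking, which is not the chi-square comparison described. So 102 does not reproduce even before clustering is considered. That is a separate and larger problem.

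**Inputs assumed for clustering.** The article gives none of these: chain size m = 5 or 10; outcome ICC (ICC_y) = 0.10 or 0.20; predictor ICC (ICC_x) as shown below.

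**Formulas.** For an association, the variance inflation is approximately

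D = 1 + (m − 1) × ICC_y × ICC_x.

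The true error of a nominal two-sided 5% test is 2 × [1 − Φ(1.96/√D)]. Setting ICC_x = 1 (predictor constant within a chain) gives the familiar D = 1 + (m − 1) × ICC_y, which is also the form for a single prevalence or mean. A predictor perfectly balanced within chains has ICC_x = −1/(m − 1), so D = 1 − ICC_y.

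| m | ICC_y | ICC_x = 0.20: D, true error | Constant in chain: D, true error | Balanced in chain: D, true error |
|---|---|---|---|---|
| 5 | 0.10 | 1.08, 5.9% | 1.40, 9.8% | 0.90, 3.9% |
| 5 | 0.20 | 1.16, 6.9% | 1.80, 14.4% | 0.80, 2.8% |
| 10 | 0.10 | 1.18, 7.1% | 1.90, 15.5% | 0.90, 3.9% |
| 10 | 0.20 | 1.36, 9.3% | 2.80, 24.1% | 0.80, 2.8% |

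Example, first row: 1 + 4 × 0.10 × 0.20 = 1.08; 1.96/√1.08 = 1.886; two-sided tail 5.9%.

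**Effective sample size for a single prevalence or mean.** 102/1.40 = 73 and 102/2.80 = 36.

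**Power.** Take 102 per wave, 36% against 26%, and clustering within waves only. Power falls from 33.8% to 25.5% at D = 1.40 and to 14.8% at D = 2.80. The number per wave for 90% power rises from 448 to 628 and 1,255. These figures do not allow for people or networks surveyed in both waves.

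**The case against.** - **The larger error rates fit few of the planned tests.** This stands. Error rates of 10% to 24% apply to a single prevalence or to a predictor constant within chains. Most planned association tests are neither, and a predictor such as gender, if balanced within chains, makes the ordinary test conservative. A reader might infer that all the p-values are too small. The article does not support that.
- **The pre/post direction is not known.** This stands. The abstract calls the survey a panel survey, and gain scores are planned. If the same people or networks are surveyed in both waves, ignoring the positive correlation between waves makes a simple chi-square or t-test conservative, against the effect of clustering within waves.
- **The extent of linkage is not stated.** This stands. There are several entry points, convenience sampling is used too, and participants make contact themselves. The friends and family described by a respondent need not be respondents. So the size cannot be fixed from the article.
- **The network analysis already deals with dependence.** True only for its own question. Comparing the observed network with one in which smoking is randomly distributed does not rely on independent respondents, but it corrects none of the chi-square, t or regression results.
- **Variance estimation belongs in a fuller plan.** This would answer mere silence. Here the article names its tests, even if some only as examples, and they do not fit its stated sampling and hypothesis.

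**Conclusion.** The point holds, with limits. Deliberate snowball recruitment, expected similarity within networks and tests that assume independence do not fit together. For the second research question, p-values will tend to be too small for predictors that cluster in networks. Under the assumed inputs, the true error is about 6% to 9% at a predictor ICC of 0.20, 10% to 24% at the extreme of a predictor constant within chains, and about 3% to 4% for a predictor balanced within chains. The direction for clustered predictors follows from the article's own reasoning; the size rests entirely on assumed chain sizes and ICCs.

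No direction can be claimed for the pre/post comparison, and the simulated-network test for the first research question is not affected. A reader might also infer that published confidence intervals are too narrow. The article specifies none, so this applies only to intervals later derived from these methods.

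**What to change.** 1. Record each respondent's referrer and recruiting site. The instruments already ask about friends, family and household members. Referral links not captured at recruitment are hard to recover later.
2. For the second research question, replace the simple chi-square, t and ordinary regression analyses with models that use small-sample-corrected cluster-robust standard errors or a random effect for recruitment chain or household. Network permutation tests are an alternative, and may suit better if chains, households and organisations overlap in one connected community.
3. In the sample size section, state that the power figure makes no allowance for dependence between respondents, and show power over a range of design effects. The article gives no basis for fixing a single value.
4. For the pre/post comparison, state whether the same people are surveyed twice, and allow for both the repeat responses and the network links.

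**Cost.** One or two extra fields and a change of model. Intervals will usually be wider, and a small-sample correction is needed if chains are few. Referral data need care in a small community with participants from age 12. None of this removes the selection bias of non-probability sampling, which should be listed among the limitations; these now discuss only the lack of a randomised control group and the weaker pre/post design.
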